### Overview of study design

West China hospital receives the most patients with PGASAH in western of China. This study is a prospective, single-centre, observer-blinded, randomized controlled trial with stratification according to the patient’s age, gender, Hunt & Hess grading and the size of aneurysm. Ninety-nine patients meeting the criteria will be randomly assigned into three treatment groups. The early surgery group will receive operation within 3 days after onset of SAH, the intermediate surgery group from days 4 to 7, and the late surgery group after day 7 post-SAH.

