### Sample size

The rate of unfavorable outcomes in patients with PGASAH is approximately 50% [22]. A statistically significant difference in unfavorable outcomes between the different surgery times is 30%, which would have statistically significant differences. A sample size of 88 will be required with 80% power and a 5% (2-sided) significance level. On consideration of the loss to follow-up, the sample size will be increased to 99 subjects.

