### Randomization

Minimization, a kind of balance randomization method, will be used in this trial. Characteristics of patients who meet the selection criteria will be submitted to random analyst. After the data is entered into a computer, patients will be randomly divided into an early, intermediate or late surgery group using specialized minimization software. Once random allocation has been determined, groups cannot be changed. Stratified randomization will be employed. Four stratification factors will be applied to achieve balanced randomization: 1) patient’s age, 2) gender, 3) Hunt & Hess grading and 4) the size of aneurysm.

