### Statistical analysis

Intention-to-treat (ITT) analysis and per-protocol (PP) analysis will be performed. The level of significance required for 80% power and a 5% (2-sided) significance level will be used. All data will be analyzed by the statistical analysis using Statistical Package for Social Sciences software (SPSS), version 17.0. Quantitative variables will be analyzed using t-test. Chi-square test and Fisher’s exact test will be used to analyze categorical variables. To analyze the outcome at 6 months after surgery, a comparison between groups will be made using the Mann–Whitney U-test and the significance of observed differences in outcome will be assessed with the Fisher’s exact test. Survival analysis will be further compare mortality between groups. Logistic regression will be used to adjust the effect of multivariable.

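### Allocation is minimised on four factors, but the tests named for the 6-month outcome ignore them; if the factors are prognostic, those tests are conservative and lose power

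*Protocol article*

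**What the plan says.** In the Protocol article, the Randomization section uses minimisation to allocate patients to three surgery-timing groups and adds: "Four stratification factors will be applied to achieve balanced randomization". The factors are age, gender, Hunt & Hess grade and aneurysm size; the Overview of study design lists the same four. The Follow-up section makes two scales primary at 6 months, the Extended Glasgow Outcome Scale (GOSE) and the modified Rankin Scale (mRS).

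For the outcome at that time point the Statistical analysis section states that "a comparison between groups will be made using the Mann–Whitney U-test", and it assigns the significance of outcome differences to Fisher's exact test. A later sentence reads "Logistic regression will be used to adjust the effect of multivariable". It does not say which covariates enter, which outcome is modelled or what role the model has. Survival analysis of mortality is mentioned without covariates.

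No test carries the label primary. That Mann–Whitney and Fisher bear on the primary outcomes follows from their being the tests named for the 6-month outcome. The article gives no figure for how strongly any of the four factors predicts outcome.

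**The concern.** Minimisation makes the arms alike on the chosen factors. If those factors predict outcome, the difference between arms varies less from one possible allocation to another than it would under unrestricted randomisation. Mann–Whitney and Fisher take no account of this. They judge the observed difference against too wide a reference distribution, so the true type I error falls below 5% and power falls with it.

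The authors themselves treat grade as relevant to prognosis: the Background faults an earlier timing study for leaving clinical grade out of account. Balancing on grade and then leaving it out of the named comparison is hard to square with that.

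There is also a practical risk. An unadjusted test and an adjusted model with open content can disagree, and the article does not say which of them decides.

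**Working it through.** **1. The plan's own figure.** Inputs from Sample size: 50% unfavourable outcome, a 30-point difference (read as absolute), 80% power, 5% two-sided. With p = 0.5 in both variance terms:

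n per group = 2 × p(1 − p) × (1.960 + 0.842)² / 0.30² = 0.5 × 7.85 / 0.09 = 43.6, so 44, and 2 × 44 = 88.

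This matches the stated figure ("A sample size of 88 will be required with 80% power and a 5% (2-sided) significance level") as a two-group total. The increase to 99 corresponds to about 11% loss: 88 / 0.89 = 98.9. The trial has three arms. With equal allocation (assumed; the ratio is not stated) that gives 99 / 3 = 33 per arm randomised and 88 / 3 ≈ 29 evaluable. At 33 per arm, pairwise power for 50% v 20% is about 73% by the normal approximation and 66% by Fisher's exact test. The use of a two-group total for three arms is a separate matter; here it shows only that there is no power to spare.

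**2. Simulation at 99 patients.** Three arms, minimisation on four binary factors with assignment probability 0.8, one pairwise comparison, 3,000 runs per setting. The Monte Carlo standard error is about 0.4 points for error rates and 0.6 to 0.9 for power. Assumed odds ratios (age / gender / grade / size): moderate 1.5/1/2.5/1.5, strong 2/1.2/4/2, very strong 4/2/6/4. Power is at a conditional odds ratio of 4 for treatment.

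| | None | Moderate | Strong | Very strong |
|---|---|---|---|---|
| Type I error, Mann–Whitney | 5.5% | 4.1% | 2.9% | 1.7% |
| Type I error, Fisher | 4.1% | 3.3% | 2.3% | 2.0% |
| Type I error, rank ANCOVA on the four factors | 5.7% | 5.2% | 5.2% | 5.7% |
| Power, Mann–Whitney | 88.5% | 84.6% | 80.2% | 69.7% |
| Power, rank ANCOVA | 88.2% | 86.5% | 85.8% | 83.6% |
| Power lost by not adjusting (points) | −0.3 | 1.9 | 5.6 | 13.9 |

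Compare tests within a column only, because the marginal treatment effect shrinks as the factors strengthen.

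**3. Is balancing the cause?** Under permuted 1:1:1 allocation with no balancing on the factors, Mann–Whitney error stayed at 5.4, 5.0, 4.9 and 4.1%. Most of the shortfall therefore comes from testing as if allocation were unrestricted.

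**4. Dichotomised outcome.** Part of Fisher's low error is discreteness: its exact size at 33 per arm is about 3.6% with no covariate involved. Setting that aside, Pearson chi-square power was 75.6, 70.3, 64.2 and 53.5%, against 76.7, 73.1, 70.9 and 66.7% for a logistic score test adjusted for the factors. The adjusted test's own error was 5.7 to 6.7%, so not all of that gap is real.

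**5. Repeat at 88 evaluable patients.** With no, moderate and strong factors, Mann–Whitney error was 5.6, 3.6 and 3.2% and power 79, 76 and 69%. A rank-based adjusted test had error of 5.6, 4.4 and 5.4% and power of 78, 78 and 77%. The power lost is −1, 2 and 8 points.

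**6. The obvious replacement model.** A proportional-odds model with the four factors, tested by likelihood ratio at 87 to 88 patients, gave type I error of about 6.0 to 6.8% pairwise and 6.5 to 7.3% for the three-arm test. It exchanges a conservative error for an anti-conservative one.

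**The case against.** The article does plan covariate adjustment, and a condensed article need not list the covariates. That is right, and the missing list is not the point. The point is that the tests the article does name for the 6-month outcome cannot take the factors in, and the logistic sentence does not change which tests those are. It is also right that calling Mann–Whitney and Fisher the primary tests would go beyond the text.

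The effect depends on prognostic strengths that the article does not give. That stands in full. With non-prognostic factors nothing is lost, and a loss of 6 points or more needs strong ones. A reader might infer a fixed penalty of 8 points or so; the documents do not support any single figure.

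A reader might also infer that ignoring the factors inflates false positives and so threatens validity. The simulations show the reverse: the error rate falls. This is an argument about efficiency.

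Finally, adjustment by a standard ordinal model brings its own miscalibration at this size. That stands too, and it shapes the recommended p-value.

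**Conclusion.** The mismatch between allocation and the named 6-month tests is real, and it matters in proportion to how prognostic the four factors are. From none to very strong, Mann–Whitney error goes from about 5.5% to 1.7% and the power lost from about 0 to 14 points: about 2 for moderate factors and 6 to 8 for strong ones. These figures rest on assumed odds ratios, binary factors, equal allocation and, in the 99-patient simulation, an assignment probability of 0.8; the article specifies none of these. A positive result from the plan as written would not be undermined on this ground. A negative one could partly reflect power given away. The change is worth making, but it is not a condition for the trial's validity.

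**What to change.** In Statistical analysis:

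- Make the main 6-month comparison of each primary scale (GOSE and mRS) one adjusted for age, gender, Hunt & Hess grade and aneurysm size.
- Take the p-value from a rank-based covariate-adjusted test (for example, regress the ranked outcome on arm and the four factors) or from a re-randomisation test that reruns the minimisation. Do not take it from a proportional-odds likelihood-ratio test.
- Report covariate-adjusted common odds ratios with 95% CIs as the effect estimate.
- Put the same four factors in the logistic and survival models.
- Keep the unadjusted Mann–Whitney and Fisher tests as sensitivity analyses.

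The cost is small. The factors are already collected for allocation, so no new data are needed. The estimate takes on a proportional-odds assumption and becomes a conditional odds ratio. Almost no power is lost if the factors are not prognostic (88.2% v 88.5%, and 78% v 79%, in the two simulations). A re-randomisation test also needs the minimisation settings, including any random element, on file. The Abstract speaks of assignment in the past tense and the Overview in the future; if allocation has begun, make this a dated amendment before anyone sees outcomes by arm.

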## Discussion

Many neurosurgeons are reluctant to treat patients with PGASAH, because the disease burden higher mortality, higher disability, more medical care costs, and higher medical risks. Although neurosurgery has rapidly developed in recent years, the prognosis of PGASAH remains dismal. Controversy surrounding the optimal timing of surgery for PGASAH still continues. In spite of many difficulties, we carried out the trial on the consideration of the following reasons: First, although many neurosurgeons have done much work on the timing of surgery for PGASAH, there is a lack of randomized controlled trial focusing specifically on this condition. Second, no optimal timing, no better surgical intervention outcome. The prognosis for PGASAH is poor, owing to the nature of the disease, but also contributed to the timing of surgery. Third, there has been great progress both in neurosurgical clipping and endovascular coiling. The comparability of treatment outcome between neurosurgical clipping and endovascular coiling should be suspected, if the outcome of PGASAH that yield by the optimal surgical timing is lacking. In a similar way,the lack of optimal timing for coiling [25] may prevent the clinical outcomes of these two treatments from being comparable.

As we know, the prognosis of PGASAH is affected by many factors. The timing of surgery for PGASAH plays an important role in patient outcomes. The factors that cause the initial poor condition of patients with PGASAH are still not clear. Few studies have focused on ICP of the PGASAH. What is the range of ICP in PGASAH? And whether there is a relationship between the elevated intracranial pressure (EICP) and the PGASAH? The peak value of ICP that patients with PGASAH can withstand, the duration of this EICP and the ideal ICP in optimal timing for surgery are all variables we wish to elucidate from our study. The study considerations of our trial are presented in Figure 1.

**Figure 1 F1:**
[figure not shown]
The study considerations of our trial.

This trial was elaborately designed to avoid several forms of bias and improve accuracy. The experience of presciously authors was noted and was merged into our design of the trial [19-21]. We will record all treatment results and surgical results, but only treatment results will be utilized for analysis. This will avoid selection bias, because all treatment results will include patients that may die from rebleeding, vasospasm or other complications, when awaiting surgery, especially those patients assigned to the intermediate or late surgery groups. Patients in intermediate or late surgery groups will receive emergency surgery when space-occupying hematoma, midline shift and emergency surgery indications are confirmed. Bias will be solved through the use of ITT analysis.

Although previous reports have demonstrated that patients in poor condition on admission within 6 hours after the onset of SAH achieved better outcomes than patients admitted later [12,26], this trial will enroll all the patients with PGASAH on admitted within 72 hours. As one of the largest hospitals in China, the number of patients admitted within 6 hours after the onset of SAH was relatively small in our department. More patients are transferred from other cities, even from the outlying areas in the west of China, and which takes time. The trial was not designed to include a small number of patients, but to include the overwhelming majority of the patients.

Neurosurgeon experience is an important factor in outcome after SAH. More than 4,000 surgeries are completed in our Department of Neurosurgery every year. Every neurosurgeon participating in the trial has accumulates experience of more than 200 neurosurgical clippings yearly, thus ensuring that every surgery will be performd to a high standard.

According to previous report, the major risk of rebleeding after SAH presented within the first 6 to 12 hours, and the risk of ultra-early rebleeding was even higher for patients with PGASAH [10]. Many neurosurgeons attempted to performed early or ultra-early/urgent surgery on the patients with PGASAH [21,27], so that prevented rebleeding. However, some authors detected the incidence of rebleeding with a higher frequency [28,29], even as high as 89% [30], during emergency cerebral angiography within 6 hours after initial SAH. As we know, the frequence of rebleeding will increase during cerebral angiography, because the thrombus at the aneurysm dome is still fragile only a few hours after initial SAH, and the injection of contrast medium may suddenly increase the intra-arterial pressure. Indeed, ultra-early surgery did not improve the rebleeing rates and clinical outcomes of patients [31,32]. Therefore, whether the patients with PGASAH benefit from early or ultra-early/urgent surgery is still unclear.

In conclusion, evidence for the optimum timing of surgery is still insufficient. We will evaluate the prognosis of patients with PGASAH receiving surgery at different times, aiming to identify optimum timing for intervention in these cases.

## Abbreviations

SAH: Subarachnoid hemorrage; PGASAH: Poor grade aneurysmal subarachnoid hemorrhage; EVD: External ventricular drain; GOSE: Extended glasgow outcome scale; mRS: Modified rankin scale; BMEC: Biological and medical ethics committee; CRF: Case report form; QMB: Quality monitoring board; CT: Computed tomography; DSA: Digital subtraction angiography; MRA: MR angiography; CTA: CT angiography; AE: Adverse events; SAE: Serious adverse events; ITT: Intention to treat; SPSS: Statistical package for the social sciences; EICP: Elevated intracranial pressure.
